## Emergency unblinding

The unblinding envelope provided to the investigator should only be opened in emergency situations. If unblinding is needed, the investigator must inform the sponsor before unblinding the subject or subjects. If the randomization is unblinded, the sponsor must be informed immediately over the phone, and the reason and date of the unblinding must be recorded in a separate document. The opened unblinding envelope must be dated and signed by the investigator.

## Management of overdose

The experimental drug has not previously been administered to humans. If overdose is observed, the investigator must admit the subject for monitoring of adverse events and appropriate symptomatic treatment.

- Experimental drug:

1. Overdose of this drug has not been reported during clinical studies. No severe toxicity was seen after administering this drug to 12 patients at ≤2400 mg / day for ≤10 days.
2. Symptoms of NSAID overdose usually include malaise, somnolence, nausea, vomiting, and upper abdominal pain. These symptoms can be treated with supportive therapy. Gastrointestinal bleeding may occur, and rarely also hypertension, acute renal failure, respiratory depression, and coma.
3. Symptomatic and supportive therapy is standard, and there is no specific antidote.
4. Symptom onset within 4 hours of use or after very excessive use may be managed with induced vomiting, activated charcoal (60-100 g for adults, 1-2 g / kg for children), and osmotic laxatives.
5. Hemodialysis, forced urination, alkalization of urine, and hemoperfusion are not useful due to the high protein binding rate of celecoxib.

- Comparator:

1. Overdose of this drug has not been reported during clinical studies. No severe toxicity was seen after administering this drug to 12 patients at ≤2400 mg/day for ≤10 days.
2. Symptoms of NSAID overdose usually include malaise, somnolence, nausea, vomiting, and upper abdominal pain. These symptoms can be treated with supportive therapy. Gastrointestinal bleeding may occur, and rarely also hypertension, acute renal failure, respiratory depression, and coma.
3. Symptomatic and supportive therapy is standard, and there is no specific antidote.
4. Symptom onset within 4 hours of use or after very excessive use may be managed with induced vomiting, activated charcoal (60-100 g for adults, 1-2 g / kg for children), and osmotic laxatives.
5. Hemodialysis, forced urination, alkalization of urine, and hemoperfusion are not useful due to the high protein binding rate of celecoxib.

## Evaluation and treatment of subjects after study termination

Subjects will receive standard therapy according to the institution, the generally accepted therapeutic guideline, and the individual medical need of the subject for any adverse events occurring during the study period.

# Study procedure and evaluation

The study procedure and evaluations will be conducted as detailed below:

## Evaluation schedule

A general summary of the study procedure is shown in the study flow chart (Appendix 1). All visits must be conducted according to the pre-determined schedule. The study duration for each subject is 12-14 weeks and consists of the following evaluations:

- - Screening and washout period: 0 - 2 weeks (Day -14 - Day 1).
  - Treatment & F/U period: 12 weeks (Day 1 - Day 84).

The visit schedule during the study consists of 3 visits, including 1 pre-treatment screening visit. Randomization and study drug distribution will be conducted at visit 2, and the last visit will be conducted 12 weeks after the first day of the investigational product administration.

Additional visits may be conducted if adverse events occur.

#### Visit 1: Screening visit (Day -14 - Day 1)

At visit 1, the investigator will obtain consent from all subjects and evaluate whether they meet all the inclusion criteria and do not meet any of the exclusion criteria. If deemed suitable for this study, the investigator will conduct the following procedures and evaluations for each subject:

- - Obtain signed consent.
  - Assign screening number.
  - Document demographic data.
  - Document item data.
  - Physical examination (including weight measurement).
  - Vital signs (blood pressure, pulse rate, respiration rate).
  - Take blood sample.
  - Pregnancy test (for women of childbearing potential).
  - Confirm medication history.
  - Check pre-treatment adverse event.
  - Instruct for washout if the subject is on contraindicated medication.
  - (If applies) book visit 2 on Day 1 within 14 days of visit 1.
  - Fill out the case report form.

#### Visit 2: Randomization visit (Day 1)

Visit 2 will be conducted on Day 1. The investigator will conduct the following procedures and evaluations for each subject:

- - Reconfirm the fulfillment of inclusion / exclusion criteria.
  - Conduct the pain VAS evaluation.
  - Conduct the LDQ evaluation.
  - Randomization.
  - Record all new adverse events and / or changes in pre-existing adverse events.
  - Record all co-administered drugs and / or changes in pre-existing co-administered drugs.
  - Distribute the GSRS and EQ-5D surveys and ask the subjects to answer them.
  - Distribute the investigational products.
  - Explain how to use the ancillary and rescue drugs, and how to fill out the subject log.
  - Distribute the ancillary and rescue drugs.
  - Confirm subject log completion and remind to bring the log at visit 3.
  - Book visit 3: the visit should be 84 days after visit 2 (Day 84 - 87).
  - Fill out the case report form.

#### Visit 3 (Day 84 - 87)

The following procedures and evaluations will be conducted:

- - Record all new adverse events and / or changes in pre-existing adverse events.
  - Record all co-administered drugs and / or changes in pre-existing co-administered drugs.
  - Conduct the pain VAS evaluation.
  - Conduct the LDQ evaluation.
  - Distribute the GSRS and EQ-5D surveys and ask the subjects to answer them.
  - Physical examination.
  - Vital signs (blood pressure, pulse rate, respiratory rate).
  - Blood sample collection.
  - Collect the unused investigational products, ancillary drugs, and rescue drugs.
  - Collect the completed subject log.
  - Complete the case report form.

#### Early termination visit

During this visit, the following procedures and evaluations will be conducted, as per visit 3:

- - Record the reason for early termination.
  - Record all new adverse events and / or changes in pre-existing adverse events.
  - Record all co-administered drugs and / or changes in pre-existing co-administered drugs.
  - Conduct the pain VAS evaluation.
  - Conduct the LDQ evaluation.
  - Distribute the GSRS and EQ-5D surveys and ask the subjects to answer them.
  - Physical examination.
  - Vital signs (blood pressure, pulse rate, respiratory rate).
  - Blood sample collection.
  - Collect the unused investigational products, ancillary drugs, and rescue drugs.
  - Collect the completed subject log.
  - Complete the case report form.

#### Additional visit

Additional visits may be conducted, if required, for the follow-up evaluation of adverse events, etc. The evaluation criteria for the additional visits will be subject to the investigator’s judgement, but may include the following:

- - Record all new adverse events and / or changes in pre-existing adverse events.
  - Record all co-administered drugs and / or changes in pre-existing co-administered drugs.
  - Physical examination.
  - Vital signs (blood pressure, pulse rate, respiratory rate).
  - Blood sample collection.
  - Complete the case report form.

## Demographic information and other baseline evaluations

Demographic and other baseline information, including the following variables, will be evaluated:

- - Demographic information, such as age and gender.
  - Information regarding health status, such as current and past medical history.
  - Past and present medication history (including co-administration of low dose aspirin).
  - Participation in other clinical trials (within 30 days of screening).
  - Weight.
  - Surveys related to efficacy evaluation (LDQ, GSRS, pain VAS, and EQ-5D).

## Safety evaluation

The safety of the investigational products will be evaluated by recording, reporting, and analyzing the subjects’ baseline comorbidities, adverse events, physical examination results (including vital signs), and laboratory test results. The severity of the adverse events that may occur after the administration of the investigational products will be evaluated using the CTCAE (Common Terminology Criteria for Adverse Events).

After consent has been given, a comprehensive evaluation of drug toxicity, including the adverse events experienced by the subjects, will be conducted throughout the duration of the study. All personnel involved in the study must report all adverse events reported by the subjects and recognized by the investigator (refer to section 6.3.1.2, “Reporting and evaluation of adverse events”). Refer to Sections 6.3.1.4 and 6.3.1.5 for the deadline for adverse events reporting.

## Adverse events

## Definition of adverse events

#### Adverse events

Adverse events include all harmful and unintended signs (including laboratory test results), symptoms, or diseases occurring in subjects who have received the investigational products. The adverse events need not be causally related to the investigational products. In cases of surgical or diagnostic treatment, the causative condition or disease, rather than the treatment itself, will be considered as an adverse event. In cases of death, the cause of the death will be considered an adverse event, and the death will be considered an outcome of the said adverse event.

The following items are not included as adverse events:

- - The disease or disorder being investigated by this study.
  - An asymptomatic overdose of the investigational products or co-administered drugs.
  - Medical or surgical treatment (the causative condition for the treatment is considered an adverse event).
  - A disease or condition existing before, or found at the start of, the study that does not worsen during the study period.
  - Cases in which no undesirable medical events occurred (e.g. hospitalization for pre-scheduled surgery for a pre-existing condition that did not worsen after administration of the investigational product).

#### Causal relationship between the drug and adverse events

Evaluation of an association between the administration of the investigational product and adverse events (definitely related, probably related, possibly related, unlikely to be related, not related, not assessable) will be performed clinically, based on all information obtainable at the time of the case report completion.

#### Definitely related

An association between the investigational product and an adverse event is clear and fulfills all of the criteria for ‘Probably related’ in addition to the criteria below:

- - Recurrence at resumption of administration (if applicable).
  - The adverse event is consistent with known information regarding the investigational product or drugs of the same class as the investigational product.

#### Probably related

This category includes clinical events such as laboratory abnormalities that are not associated with comorbid diseases, other drugs, and chemicals that all have logical temporal continuity with investigational product administration, lead to clinically relevant results after investigational product discontinuation, and fulfill the following criteria:

- - Evidence of investigational product administration.
  - Logical temporal order between investigational product administration and the adverse event incidence.
  - The adverse event can be explained more logically by exposure to the investigational product than by other possible reasons.
  - A disappearance or alleviation of the adverse event after investigational product discontinuation or dose reduction.

#### Possibly related

Clinical events such as laboratory test abnormalities that can be explained by co-morbid diseases, other drugs, or chemicals, but which also show logical temporal continuity with investigational product administration (although not accompanied by information on drug discontinuation) and fulfill the following criteria:

- - Evidence of investigational product administration.
  - Logical temporal order between investigational product administration and the adverse event incidence.
  - An adverse event that is equally likely to be due to the investigational product as to other possible causes.
  - An adverse event that disappears or is alleviated by investigational product discontinuation or dose reduction.

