#### Unlikely to be related

Generally, the cases listed below are considered unlikely to be related:

- - Evidence of investigational product administration.
  - A higher possibility that an adverse event is due to reasons other than investigational product administration.
  - Negative or dubious results after investigational product discontinuation or dose reduction (if applicable).
  - Negative or dubious results after investigational product re-administration.

1. **Not related**
   - The subject failed to receive the investigational product.
   - No logical temporal order between investigational product administration and the adverse event incidence.
   - The presence of other evidence that can clearly explain the reason for the adverse event incidence (e.g. bleeding from a surgical site).
   - Not likely (e.g. the patient collided with a motorcycle, but there is not enough proof that the investigational product causes enough loss of proprioception to cause the event, or a cancer that is found days after investigational product administration).

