#### Safety reporting to government authorities, the institutional review board (IRB), and the investigator

If the investigator reports an SAE (in particular, death) in a subject to the IRB, the report must follow the SAE reporting criteria of the said IRB. According to the ICH GCP, the sponsor must notify the investigator if “a case that may negatively affect a subject’s ability to undergo the study or changes the IRB approval status on the continuation of the study” occurs. In particular, according to the relevant regulations, the sponsor must inform the investigator of any suspected unexpected serious adverse reaction (SUSAR). The investigator must store safety-related reports within the investigator’s site file. Safety reporting must comply with local regulations for safety reporting to the investigator. If mandated by law, the sponsor can directly report to the IRB, and such a report will be documented. If not mandated by law, the investigator must directly report the safety information supplied by the sponsor to the IRB, and copies of all communication records regarding this issue must be kept within the investigator’s site file. The sponsor must report safety-related issues to the health authorities, according to the relevant law and regulations. For local studies, SUSAR reports must be conducted according to the Pharmaceutical Affairs Act. According to this Act, any SUSAR that is fatal or life-threatening must be reported to the MFDS within 7 days of the sponsor becoming aware of it, and, in such a case, the sponsor must report the details of the SUSAR within 8 days of the first report date. All other SUSARs must be reported within 15 days of the sponsor being made aware of them.

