- Ancillary and rescue drug use after 12 weeks of oral administration of the investigational product, the average number of days used, the average daily amount used (total amount used / total number of days used), and the average amount of use during study participation (total amount used / study duration): the number and proportion of subjects who use ancillary or rescue drugs during the 12 weeks of investigational product administration are presented for each treatment arm. The between-group difference will be tested for significance using the Chi-square test or Fisher’s exact test. Descriptive statistics (sample size, mean, standard deviation, median, min, max) will be presented for the average number of days of ancillary or rescue drug use, the average amount used per day (total amount used / total number of days used), and the average amount used during the study period (total amount used / duration of study participation) in each treatment arm. The between-group difference in the average will be tested for significance using the independent two-sample t-test or the Wilcoxon rank sum test.
- The incidence, frequency, and characteristics (clinical presentation, severity, result, etc.) of adverse events after 12 weeks of oral administration of the investigational product: the number and proportion of subjects that experienced all adverse events, SAEs, and adverse events leading to study discontinuation during the 12 weeks of investigational product administration, as well as all adverse events, SAEs, and adverse events leading to study discontinuation that are related to the investigational product are presented for each treatment arm. The between-group difference in proportion will be tested for significance using the Chi-square test or Fisher’s exact test. The number of all adverse events and adverse events associated with investigational product, the severity and seriousness of these events, the treatment, and the results of the events will also be presented. The number and proportion of subjects, as well as the number of events for all adverse events and adverse events associated with the investigational product, as per MedDRA or WHOART SOC, and the PT, will also be presented for each treatment arm.

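### The 'Possibly related' definition contradicts itself: it admits events with no discontinuation information, then requires improvement on discontinuation or dose reduction

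*Protocol*

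**What the plan says.** Protocol section 6.3.1.1 gives six causality categories, each with its own list.

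- **Possibly related.** The lead-in describes events that another cause could explain but that fit the timing of treatment, and it adds "although not accompanied by information on drug discontinuation) and fulfill the following criteria". The fourth criterion that follows is "An adverse event that disappears or is alleviated by investigational product discontinuation or dose reduction".
- **Probably related.** The fourth criterion is "A disappearance or alleviation of the adverse event after investigational product discontinuation or dose reduction".
- **Definitely related.** The event "fulfills all of the criteria for ‘Probably related’ in addition to the criteria below". One added criterion is "Recurrence at resumption of administration (if applicable"), so the rechallenge item carries a qualifier.
- **Unlikely to be related.** The matching item is "Negative or dubious results after investigational product discontinuation or dose reduction (if applicable"), again with a qualifier.

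The categories feed an analysis. In section 7.5.3, all adverse events, SAEs and events leading to discontinuation are tabulated. So is the related subset of each, down to "adverse events leading to study discontinuation that are related to the investigational product are presented for each treatment arm", and the proportions are tested between groups.

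**The concern.** A causality category should be usable for the events it describes. Here the description and the criteria exclude one another, and the two stronger categories offer no way round.

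The gap is not remote in this trial. Section 5.3.1.1 supplies an antacid throughout the study for dyspepsia attributed to the study product. The plan therefore expects drug-attributed symptoms in subjects who stay on treatment. Such an event can settle without the drug ever being stopped or reduced.

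What is at stake is the consistency of the related-event counts. Causality is assigned at each of 10 sites. Where the written rule contradicts itself, each site must choose which half to follow. A later analysis plan can decide how to group the categories, but it cannot recover which half of the rule a site applied. The investigator's follow-up duty in section 6.3.1 (monitoring of a subject's adverse event) is also worded around possible association with the product, so the same ambiguity can carry over there.

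**Working it through.** The plan states no figure on this point, so the check is one of logic: set the categories side by side, then run test events through them.

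**Step 1. What each category asks about stopping or reducing the drug**

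| Category | Response required | Qualified by 'if applicable'? |
| --- | --- | --- |
| Definitely | Improvement, inherited from Probably | No (the qualifier is on rechallenge only) |
| Probably | Improvement | No |
| Possibly | Improvement, though the lead-in says the information is absent | No |
| Unlikely | Negative or doubtful response | Yes |

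The qualifier was available to the authors and was used twice. It does not appear on the improvement criterion of any positive category.

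**Step 2. Possibly related taken alone**

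- If the lead-in is defining (information on stopping is absent), no event can also show improvement on stopping, and the category is empty.
- If the lead-in is permissive (information may be absent), an event without it is admitted by the lead-in and then fails the fourth criterion.

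Neither reading leaves the definition working.

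**Step 3. Test events**

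- *Event that resolves with study drug unchanged.* There was no stop or reduction, so no improvement on one. It fails Possibly and Probably, and therefore Definitely.
- *Fatal event.* Section 6.3.1.1 treats the cause of death as the event and death as its outcome. The event neither disappeared nor improved, so it fails the same three.
- *Event ongoing at Visit 3.* Section 6.3.1 continues follow-up until improvement or stabilisation, after study drug has ended. A response to stopping may be seen, so this event can qualify.

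For the first two, 0 of 3 positive categories are literally open.

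**Step 4. Where those events go**

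Unlikely is a poor fit, because its list includes another cause being more probable and, without a qualifier, a negative or doubtful rechallenge. Not assessable is for insufficient or conflicting information. In practice a site either overlooks the fourth criterion and records Possibly, or records Not assessable, or stretches Unlikely. Different sites can reasonably differ.

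**Step 5. With the fourth criterion removed**

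Three criteria remain: the product was taken, the timing is logical, and the product is as likely a cause as the alternatives. Both test events can then be classed as Possibly related on their merits, and the lead-in agrees with its list.

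**The case against.** The strongest reply is that these lists guide judgement. Section 6.3.1.1 says causality is assessed clinically on all information that can be obtained, and response to stopping is one of seven points to consider. The lead-in to Possibly related also gives a site textual support for using it without discontinuation information. This stands in part: many investigators would probably choose Possibly. But the general instruction does not waive the listed criteria, and a site that follows the list is not wrong either.

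Three stronger readings are tempting, and the document does not support them.

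- **Serious reactions escape expedited reporting.** A reader might infer this from "any SUSAR that is fatal or life-threatening must be reported to the MFDS within 7 days". However, every new SAE goes to the sponsor within 24 hours whatever its causality, SUSAR reporting to the authority rests with the sponsor, and nothing ties suspicion to these six categories. What remains is that the protocol provides for fatal suspected reactions while its positive categories, read literally, have no place for one.
- **The undercount can be sized.** A reader might take 20-25% dyspepsia in NSAID users (section 2.6) and 7.1% of celecoxib subjects stopping for adverse events (section 5.3.5.1). That gives 0.20 × 53 = 10.6 to 0.25 × 53 = 13.3 cases, less 0.071 × 53 = 3.8 stops, or about 6.8 to 9.5 per arm. The two rates come from different populations. The celecoxib dyspepsia rate in the same section, 8.8%, gives 0.088 × 53 = 4.7, less 3.8, or about 0.9. Neither calculation allows for temporary stops, which section 4.5.2 provides for, or for improvement seen after treatment ends. A result that moves from about 1 to about 9 with the choice of source is no estimate.
- **Probably related is also defective, and the plan must say which categories count as related.** Probably related is internally consistent, since its lead-in and fourth criterion both refer to discontinuation. Grouping for tables is commonly left to the SAP, which is not shown, and Not assessable might be counted as related there. For that reason the undercount is possible, not established.

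**Conclusion.** The point holds as an internal contradiction in Possibly related. Because Probably and Definitely carry the same requirement, events that occur and resolve on continued treatment, and fatal events, literally meet no positive category. This conclusion rests on reading the listed criteria as required, which is how the lead-in words them.

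The effect is confined to the related-AE and related-SAE tables and their between-arm tests. The counts may be inconsistent between sites and possibly too low; by how much cannot be derived from the document. The GI adverse event incidence, discontinuation due to GI events, and the all-cause AE and SAE analyses do not use relatedness, and the primary LDQ analysis is untouched. Assessors are blinded and use the same definitions in both arms. The repair is worth making because the rule is operative and correcting it costs little.

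**What to change.** In section 6.3.1.1, Possibly related, delete the fourth criterion, or replace it with: *information on drug discontinuation may be lacking or unclear*. Either change brings the list into line with its lead-in and gives events without a response to stopping a positive category to fall in. The other categories need no change for this purpose.

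The cost is a wording amendment to the protocol and to any CRF guidance that repeats the definition. It needs no new data, visits or procedures. Related-event counts may be slightly higher than under the present text.
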